## Abstract

**Background:**

Definitive chemoradiotherapy is standard of care in locally advanced cervical cancer (LACC). Both toxicity and local relapse remain major concerns in this treatment. We hypothesize that a magnetic resonance imaging (MRI) based redefining of the radiotherapeutic target volume will lead to a reduction of acute and late toxicity. In our center, chemoradiotherapy followed by hysterectomy was implemented successfully in the past. This enables us to assess the safety of reducing the target volume but also to explore the biological effects of chemoradiation on the resected hysterectomy specimen.

**Methods:**

The EXIT-trial is a phase II, single arm study aimed at LACC patients. This study evaluates whether a MRI-based exclusion of the non-tumor-bearing parts of the uterus out of the target volume results in absence of tumor in the non-high doses irradiated part of the uterus in the hysterectomy specimen. Secondary endpoints include a dosimetric comparison of dose on normal tissue when comparing study treatment plans compared to treatment of the whole uterus at high doses; acute and chronic toxicity, overall survival, local relapse- and progression-free survival. In the translational part of the study, we will evaluate the hypothesis that the baseline apparent diffusion coefficient (ADC) values of diffusion weighted MRI and its evolution 2 weeks after start of CRT, for the whole tumor as well as for intra-tumoral regions, is prognostic for residual tumor on the hysterectomy specimen.

**Discussion:**

Although MRI is already used to guide target delineation in brachytherapy, the EXIT-trial is the first to use this information to guide target delineation in external beam radiotherapy. Early therapy resistance prediction using DW-MRI opens a window for early treatment adaptation or further dose-escalation on tumors/intratumoral regions at risk for treatment failure.

**Trial registration:**

Belgian Registration: B670201526181 (prospectively registered, 26/11/2015); ClinicalTrials.gov Identifier: NCT03542942 (retrospectively registered, 17/5/2018).

## Background

Definitive chemoradiotherapy (CRT) is considered standard of care in Locally Advanced (FIGO 1B2-IVA) Cervical Cancer (LACC). Definitive CRT is a 2-steps process consisting of external beam radiotherapy (EBRT) ± chemotherapy (If possible cisplatin) and a brachytherapeutic (BT) boost. Even with the use of image-guided dose-intensified BT, local relapse arising from CRT-resistant foci is high (3y-local pelvic control rates of 73% up to 96%, depending on stage and treating center) and remains a major cause of treatment failure [1–3]. In exchange for an improved overall survival (OS), adding chemotherapy to conventional EBRT has doubled the risk of severe acute hematological and gastro-intestinal toxicity and tripled platelet toxicity [4].

Triggered off by both the high local recurrence and the toxicity rates we challenged the gold standard by introducing intensity-modulated arc therapy (IMAT) followed by C1 radical hysterectomy (HRT) [5]. This HRT allows removing CRT-resistant tumor foci [6, 7]. IMAT reduces the dose to the surrounding normal organs (organs at risk = OARs) while enabling the delivery of a simultaneously integrated boost (SIB) to the primary tumor and/or enlarged lymph nodes [8]. Such a SIB, which replaces the BT boost, maximally exploits the positive relationship between higher doses, shorter overall treatment time and tumor control [9]. The combination of IMAT and chemotherapy (if possible, cisplatin is called IMAT-C. We reported previously that using IMAT-C safely allows for a post-IMAT-C HRT. Local control and survival rates were promising and both IMAT-C and surgical related toxicity rates were low [6, 7]. Further research aiming at decreasing toxicity and increasing disease control is needed.

We hypothesize that redefinition of the target volume (TV) will lead to a further reduction of acute and late toxicity. Apart from treating the tumor (“gross tumor volume” or GTV) to the highest dose, international guidelines advise to treat organs having a risk of microscopic disease (“clinical target volume” or CTV) also to the same (or high) dose. In case of LACC, the uterus is one of these organs. Influenced by bladder and/or rectal filling and tumor shrinkage, the uterus can tilt from anteflexed to retroflexed position. Angle rotations of 30° and more are noted in up to 1/5 patients [10]. This movement of the uterus and consequently the CTV remains a major problem. Concerns about these CTV movements (with the uterine fundus being the main contributor) have lead to the use of generous margins (up to 4 cm around the uterine fundus) to create the planning target volume or PTV [11]. In this way adequate coverage of the CTV at all time is ensured. Consequently, the volume of irradiated normal tissue is large and the risk of toxicity increases. However, there is no unequivocal evidence supporting the dogma that the whole uterus should be included in the CTV [12]. This “inclusion-dogma” goes back to the pre- magnetic resonance imaging (MRI) era where one could not differentiate the tumor from the uterus. Nowadays, MRI allows discrimination of the tumor with a high level of accuracy [13, 14]. Therefore, we hypothesize that excluding the non-tumor-bearing parts from the CTV, based on the MRI, leads to significant reductions in normal tissue irradiated (OARs) with tighter PTV margins [15] and reduced toxicity. Above that, HRT post-CRT gives us the unique opportunity to explore the biological effects of IMAT-C at the resected HRT specimen.

## Methods/design

### Study design

The EXIT-trial is a phase II, single arm study. The study was initiated by the Department of Radiation Oncology in collaboration with the Departments of Radiology, Pathology, Medical Oncology and Gynaecologic Oncology (Ghent University Hospital, Ghent Belgium).

### Study objectives and endpoints

The objective of this study is to assess the safety of excluding the non-involved uterus from the TV in the definitive CRT treatment of LACC. The primary endpoint is absence of tumor in the non-involved (as determined on the pre-treatment MRI) and non-high doses irradiated part of the uterus in the hysterectomy specimen after CRT. Secondary endpoints include a dosimetric comparison of dose on the OARs when comparing study treatment plans to treatment of the whole uterus at high doses; acute and chronic toxicity, OS, local relapse free and progression free survival (PFS). A translational part of the study is discussed below.

### Inclusion/exclusion criteria

Eligible patients suffer from biopsy proven carcinoma of the uterine cervix. Following inclusion criteria should be met: locally advanced disease (FIGO IB2 or > FIGO IIB or node positive) proven by clinical examination, 18-fluorodeoxyglucose positron emission tomography scan (^18^FDG PET-CT) and MRI; no more than 2 distant metastases (other than para-aortic or inguinal lymph nodes); WHO 0–2; adequate kidney function for cisplatin, in case of inadequate kidney function cisplatin can be replaced by 5-FU or radiotherapy can be the sole therapeutic regimen; not pregnant or breastfeeding; absence of any psychological, familial, sociological or geographical condition potentially hampering compliance with the study protocol and follow-up schedule; willing and able to sign a written informed consent. Patients unable to undergo MRI for any reason are excluded.

### Interventions

Figure 1 illustrates the patient-flowchart and all trial-related procedures.

**Fig. 1 Fig1:**
[figure not shown]
Workflow per patient and situation of the different time-points for each study. DW-MRI: diffusion-weighted MRI; PTV_EXIT: planning target volume as defined within the EXIT-trial; MRI HRT: Magnetic resonance imaging of the HRT specimen; FDG-PET: 18-fluorodeoxyglucose PET scan; PTV: planning target volume; MRI: magnetic resonance imaging. C: weekly chemotherapy; RT: radiotherapy; D98: dose received in 98% of the volume. *: Imaging which requires extra effort of the patient; **: only if node-positive at diagnosis

#### Radiation treatment planning

After imaging in treatment position (standard procedure or state of the art: ^18^FDG PET-CT and MRI as described in Fig. 1) [7, 8] and fusion with the RT-planning-CT, TVs and OARs will be delineated. Planning CT (p-CT) was taken on a Toshiba 16 slice CT scanner, in supine position, using intravenous and bowel contrast. Patients were scanned with a comfortable filled bladder. Delineated OARs include small intestine, rectum, sigmoid colon, bladder and bone marrow. Per patient 2 sets of PTV (see Fig. 2) will be generated, in which the PTV of the lymph nodes (lnn), (=PTV_lnn) is identical:

**Fig. 2 Fig2:**
[figure not shown]
delineation of treatment volumes following state-of-the-art (**a** en **b**) en EXIT-trial (**a** en **c**). **a** delineation of elective lymph node areas are state-of-the-art and identical in standard treatment & the EXIT_trial. Clinical target volume (CTV) of the lymph nodes (lnn) = CTV_Lnn (yellow) = elective lnn areas (common, external and internal lnn, obturator and presacral region; inclusion of para-aortic lnn if any pelvic lnn are affected). Planning target volume (PTV) of the lnn (PTV_Lnn; blue) is created using an isotropic margin of 5 mm around the CTV_Lnn. **b** GTV of the primary tumor (GTV_prim = red): primary tumor delineated using T2 weighted MRI images (state of the art). CTV of the primary tumor (CTV_prim = blue): includes GTV_prim, whole uterus, non-affected parts of the cervix and parametria, upper vaginal 1/3 to ½ (minimal vaginal margin of 2 cm to the GTV_prim). PTV of the primary tumor (PTV_prim = purple): margin around the CTV_prim of 10 mm antero-posterior (AP); 5 mm left-right (LR) and 5 mm supero-inferior (SI)

## PTV: PTV_prim + PTV_lnn (state-of-the-art, as performed out of this trial)

**PTV_prim** is created by an anisotropic expansion around the CTV of the primary (prim) tumor (= CTV_prim) of 10 mm antero-posterior (AP); 5 mm left-right (LR) and 5 mm supero-inferior (SI). CTV_prim consists of the primary tumor delineated using T2 weighted MRI images (GTV_prim) + whole uterus + non-affected parts of the cervix and parametria + upper vaginal 1/3 to ½ (minimal vaginal margin of 2 cm to the GTV_prim).

**PTV_lnn** is created using an isotropic margin of 5 mm around the CTV_lnn (CTV of the lnn) which consists of the union of following regions: common-, external- and internal iliac lnn, obturator and presacral region and para-aortic lnn if any pelvic lnn are affected. A lymph node is considered affected when.

## PTV_EXIT: PTV_prim_EXIT + PTV_Lnn

**PTV_prim_EXIT** is created using an anisotropic margin around the CTV_prim_EXIT of 7 mm AP; 5 mm LR and 5 mm SI. CTV_prim_EXIT consists of the GTV_prim + uterus within 1,2 cm around GTV_prim [16] + non-affected parts of the cervix and parametria + upper vaginal 1/3 to ½ (minimal margin of 2 cm around the GTV_prim). The **PTV_lnn** is identical as discussed above.

A treatment plan is made for both TVs using the Raysearch planning system (RaySearch Laboratories, Stockholm, Sweden) using identical prescription and constraints as in our previously published work [7, 8]. In short, a minimal dose (D98) of 45 Gy in 25 fractions is prescribed to the PTV and PTV_EXIT. A minimal dose (D98) of 62Gy is prescribed to the GTV_prim, a minimal dose of 60Gy is prescribed to any affected lnn.

### Treatment

The patient will be treated with the “PTV_EXIT” treatment plan, in 25 fractions. All treatments will be performed on an Elekta (Crawley, UK) Synergy linac with gantry mounted Cone Beam CT option. Daily Couch setup correction will be done after pre-treatment CBCT imaging consisting of M20 Field of View (i.e. 27,7 cm in SI direction), with bowtie filter, 120KV, 40 mA and 40 ms per frame, and 0,5 rpm gantry rotation speed. If necessary, adaptive treatment planning or plan-of-the-day is allowed.

Cisplatin 40 mg/m^2^ will be administered weekly during radiotherapy. In case of inadequate kidney function or other contra-indications, 5-FU or no chemotherapy is also allowed. Within 6 to 8 weeks after ending chemoradiation, a radical hysterectomy (Cibula classification: C1) will be performed [5].

### Imaging during and after treatment

All patients will undergo MRI at fixed time points (see Fig. 1 and Table 1). The MRI before, during and 2–3 weeks after CRT are considered routine standard procedures at our hospital. The MRI at the end of the treatment and within 1 week before HRT is supplemental for the study. The first is considered essential for adequate regression pattern analysis. The last MRI allows constructing a mold (e.g. 3D printing, widely available), which will act as a 3-dimentional rendering of the pre-HRT “uterine bed” and its slope. This allows mimicking the same position and angle rotation of the uterus as within the patient, which is necessary to allow for an adequate regression pattern analysis. After HRT, the HRT specimen itself will be scanned in the same position as within the patient, using the 3D-mold. The use of the 3D-mold will allow MRI-pathology comparison.

**Table 1 Tab1:** MRI scan sequences

Timing MRI	Scan Sequence & used MRI device
Standard MRI before, during and 2–3 weeks after CRT	5 mm sagittal T2 Haste, 5 mm sagittal T2 TSE, 4 mm axial T2 TSE, 5 mm axial T1 GE, 4 mm axial DWI (b-values 0, 250, 500 and 1000 with calculated b 1400)
	at 1.5 Tesla MRI scanner (Siemens Aera, Erlangen, Germany)
Supplemental MRI at the end of treatment and pre-HRT	5 mm sagittal T2 Haste, 5 mm sagittal T2 TSE, 4 mm axial T2 TSE, 5 mm axial T1 GE, 4 mm axial DWI (b-values 50, 400 and 800 with calculated b 1400)
	at 3.0 Tesla MRI scanner (Siemens Trio or Prisma Fit, Erlangen, Germany)
Hysterectomyspecimen	1 mm coronal T2 Space with 1 mm sagittal and axial reconstructions, 4 mm axial DW (b-values 50, 250,500,750,1000 with calculated b 1400)
	at 3.0 Tesla MRI scanner (Siemens Trio or Prisma Fit, Erlangen, Germany)

*MRI* magnetic resonance imaging, *mm* millimeter, *TSE* Turbo Spin Echo, *GE* Gradient Echo, *DWI* diffusion weighted imaging

The process to create the 3D mold starts with the conversion of a set of 2D contour slices delineated on the last MRI to a 3D volume using an in-house implemented marching cubes algorithm. The 3D volume is imported into Blender, an open-source 3D graphics software package. Around the imported volume, a box is generated using Python scripts and the uterus volume is subtracted from this box. The box is cutout further to support the lower half of the uterus specimen. On the side of the box, knobs are added to enable fixation of the tissue to the mold (Fig. 3).

**Fig. 3 Fig3:**
[figure not shown]
3D-mold. Example of a 3D-mold model created in Blender. The uterus, mold and knobs are depicted respectively in white, blue and green. The mold supports the uterus specimen, while the tissue is fixated to the knobs during sugery

### Clinicopathological examination

Upon receival, the fresh specimen will be removed from the 3D-mold and will be oriented, measured and weighed. The parametrial tissues, the soft tissue margins of the cervical canal and the vaginal cuff margin will be inked blue and green, signifying the left and right side, respectively. Parametria will be removed and entirely submitted for histological examination. Next, a probe will be inserted in the endocervical canal and the uterine cavity. The uterus and cervix will be bisected into posterior and anterior halves, to allow sufficient tissue fixation. These halves will be pinned on plastic to avoid curling of the tissue. The specimen will be inspected and described. Any macroscopically visible tumor will be measured and, if larger than 10 mm, a tissue sample of about 5 × 3 × 3 mm will be snap-frozen to allow future molecular studies. The bisected specimen will then be fixed in formalin for 24 h. After fixation, the vaginal cuff and the cervix will be transversally amputated and will be serially sectioned. These perpendicular clockwise sections will allow the assessment of the relationship of the tumor to the margin. Twelve, 3, 6 and 9 o’clock correspond with the anterior, left, posterior and right side of the cervix, respectively. Transverse sections of the endocervical canal and isthmus will be submitted for histological examination as well. The uterine corpus, fallopian tubes and ovaries will be macroscopically examined for abnormalities, and representative tissue samples will be submitted for histological examination. If initial hematoxylin and eosin (HE) stained tissue sections do not reveal any tumor rest in the cervix, multiple deeper sections will be performed. Additional immunohistochemistry for p40 and Cytokeratin5 will be performed to illustrate any residual isolated tumor cells when HE slides are deemed unclear. Any residual tumor, its localization and its relation to the surgical resection margins will be described in the report.

### Radiological-histological correlation

Transfer of the clinicopathological information to the post-HRT MRI will be done in cooperation with the pathologist and radiologist. In-house developed software in RayStation 6.0 allows correlation of tumor location in between the planning CT, the MRI scanned specimen and the HRT pathology result. Initially a gray based, region of interest constraint rigid fusion is done between the specimen and the planning CT, followed by a non-rigid hybrid deformable registration. Fusion of these MRIs with the planning-CT and treatment-plan will allow to allocate the remaining tumor in or out of the high-dose irradiated field.

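### The primary endpoint is met trivially when no uterus is spared, and residual tumor is located against a planned field that may not be the one delivered

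*Protocol article*

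**What the plan says.** - **Endpoint** (Study objectives and endpoints). Success is "absence of tumor in the non-involved (as determined on the pre-treatment MRI) and non-high doses irradiated part of the uterus", judged on the hysterectomy specimen.
- **Target** (PTV_EXIT). The clinical target keeps the "uterus within 1,2 cm around GTV_prim", together with cervix, parametria and upper vagina. The planning margin is 7 mm antero-posterior and 5 mm in the other two directions.
- **Eligibility** (Inclusion/exclusion criteria). There is no condition on how far the tumor extends into the uterine body. The only imaging exclusion is inability to undergo MRI.
- **Locating residual tumor** (Radiological-histological correlation). The specimen is registered to the planning CT, rigidly and then deformably. Fusing the images with the planning CT and the treatment plan is meant to "allow to allocate the remaining tumor in or out of the high-dose irradiated field". No registration tolerance is given.
- **Delivery** (Treatment). "If necessary, adaptive treatment planning or plan-of-the-day is allowed". The article does not say which plan defines the high-dose field once a plan has been adapted.
- **Precision** (Statistical considerations). 21 patients, Wilson score interval, half width 11%, assumed proportion 98%.

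**The concern.** The trial asks whether uterus left out of the high-dose field is free of tumor. A patient can inform that question only if some uterus was in fact left out. Where tumor extent plus the retained rim covers the whole uterus, the endpoint as worded is a statement about an empty region and is true whatever the pathology shows. Such patients can only raise the success proportion, and with 21 patients each one carries weight.

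The second issue is the reference for calling residual tumor in or out of field. The endpoint wording turns on irradiation received, while the allocation rule names the planning CT and treatment plan. If a patient was treated with an adapted plan or a plan-of-the-day, the two can differ. A focus near the field edge could then be assigned by a field that was not used.

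At stake is what the final proportion means: tumor absent from uterus that was not treated to high dose, or a mixture of that with uninformative successes and foci assigned to the wrong side.

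**Working it through.** **1. The plan's own figure.** Wilson half width = z·√(p(1−p)/n + z²/4n²) / (1 + z²/n). With p = 0.98, n = 21 and z = 1.96 (95% two-sided assumed, as the level is not stated), the interval is 81.3% to 99.8% and the half width 9.2%, not 11%. An observed 20/21 (95.2%) gives 10.9%, which may be the source. The stated figure errs on the cautious side. This is a separate matter and does not bear on the present point.

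**2. How much uterus is always in the field.** Retained rim 1.2 cm plus planning margin: 1.2 + 0.5 = 1.7 cm from the gross tumor left-right and supero-inferiorly, and 1.2 + 0.7 = 1.9 cm antero-posteriorly. A uterus lying wholly within that distance has no spared part. Nothing in the eligibility criteria rules this out.

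**3. Effect of empty spared regions.** The documents give no count m of such patients, so 0 to 6 of 21 is assumed for illustration. With no failures the Wilson lower limit is n/(n + z²), where z² = 3.84:

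| m | Informative n | Lower limit, no failures | Estimate (lower limit), one failure |
|---|---|---|---|
| 0 | 21 | 21/24.84 = 84.5% | 95.2% (77.3%) |
| 2 | 19 | 19/22.84 = 83.2% | 94.7% (75.4%) |
| 4 | 17 | 17/20.84 = 81.6% | 94.1% (73.0%) |
| 6 | 15 | 15/18.84 = 79.6% | 93.3% (70.2%) |

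Counting the m patients as successes reports the first row whichever row is true.

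**4. Direction of allocation error.** Let q be the true out-of-field share of residual tumors and e a symmetric misallocation rate (both assumed). The observed out-of-field share is q(1−e) + (1−q)e.

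- q = 2%, e = 5%: 0.019 + 0.049 = 6.8%.
- q = 2%, e = 10%: 0.018 + 0.098 = 11.6%.
- q = 10%, e = 5%: 0.095 + 0.045 = 14%.
- q = 10%, e = 10%: 0.090 + 0.090 = 18%.

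When most residual tumor is in the field, symmetric registration error adds apparent failures.

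**5. Planned against delivered field.** Setting the Treatment section beside the correlation section gives these routes. Tumor in uterus planned as spared but in fact irradiated may be sterilised, which scores as a success. If it survives, it scores as a failure of sparing that did not take place. Tumor planned in field but not covered by the delivered field is labelled in field and is not counted as a failure. The documents give no frequencies, so no net direction follows.

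**The case against.** **Not a stated rule.** The article nowhere says that a patient without spared uterus is a success, and treating her as not evaluable is an equally natural reading. Evaluable-set rules are often left to the full protocol or analysis plan, which are not shown. This stands in part: automatic success is an inference. The point is that the endpoint and eligibility, as worded, allow it. Likewise, a reader might infer that unresected patients silently drop out, but no section says so.

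**Planned-field scoring is defensible.** The objective is to test exclusion from the target volume, which is a planning strategy. That is fair, but the endpoint is worded in terms of dose irradiated, and once plans are adapted there is more than one planned field.

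**Safeguards exist.** An MRI within a week before surgery, a 3D mold reproducing uterine position and angle, an MRI of the specimen in that mold before bisection and fixation, and joint work by pathologist and radiologist all limit localisation error. This stands. They do not settle which plan is the reference, nor what happens with an empty region.

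**Stronger readings to avoid.** A reader might infer that scoring errors in general lean towards safety. Steps 4 and 5 do not support that; only the empty-region case runs one way. A reader might also take the Background statement "Angle rotations of 30° and more are noted in up to 1/5 patients" to mean that about 21 × 1/5 = 4 patients are mis-scored. Rotation shows that the fundus moves, not that it enters the field, and the article does not say how long a rotation lasts over 25 fractions. The same figure gives no count of empty regions or of unresected patients.

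**Conclusion.** The concern holds in limited form. As worded, the primary endpoint can be met by patients who carry no information on it, and this bias has one direction. Its size is unknown because the documents give no count. Under the assumed 2 to 6 of 21 patients, the lower limit for an apparently perfect result falls by 1.3 to 4.9 percentage points (84.5% to between 83.2% and 79.6%). No success threshold is stated, so no stated decision changes; what changes is the strength of the safety claim. Separately, the reference field is ambiguous where plans were adapted, with error of unknown direction and size. Both points should be settled before analysis. Neither invalidates the design.

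**What to change.** 1. **Study objectives and endpoints; Statistical considerations.** Make the primary denominator patients with a hysterectomy specimen and a non-empty spared uterine region. Report the spared volume per patient and the number with none. Add a sensitivity result with unresected patients counted as failures.
2. **Radiological-histological correlation.** Define the high-dose field from the plan or plans actually delivered to each patient, by one rule applied to everyone regardless of pathology. A rule that differs by outcome would itself introduce bias.
3. **Same section.** Record and lock the location of each residual focus before the dose is overlaid. State the registration error, and add a sensitivity analysis in which foci within that error of the field edge count as out of field.

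None of this alters treatment. The cost is some analysis time and a smaller denominator: with no failures the 95% half width goes from 7.7% at 21 patients to 8.4%, 9.2% or 10.2% at 19, 17 or 15. At the planning value of 98%, 17 evaluable patients still give 10.7%, inside the stated 11%; 16 give just over 11%.
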